# Study protocol of the HYPER-LIV01 trial: a multicenter phase II, prospective and randomized study comparing simultaneous portal and hepatic vein embolization to portal vein embolization for hypertrophy of the future liver remnant before major hepatectomy for colo-rectal liver metastases

**DOI:** 10.1186/s12885-020-07065-z

**Published:** 2020-06-19

**Keywords:** Liver metastases, Portal vein embolization, Venous deprivation, Major hepatectomy, Colo-rectal cancer

## Abstract

**Background:**

In patients undergoing major liver resection, portal vein embolization (PVE) has been widely used to induce hypertrophy of the non-embolized liver in order to prevent post-hepatectomy liver failure. PVE is a safe and effective procedure, but does not always lead to sufficient hypertrophy of the future liver remnant (FLR). Hepatic vein(s) embolization has been proposed to improve FLR regeneration when insufficient after PVE. The sequential right hepatic vein embolization (HVE) after right PVE demonstrated an incremental effect on the FLR but it implies two different procedures with no time gain as compared to PVE alone.

We have developed the so-called liver venous deprivation (LVD), a combination of PVE and HVE during the same intervention, to optimize the phase of liver preparation before surgery. The main objective of this randomized phase II trial is to compare the percentage of change in FLR volume at 3 weeks after LVD or PVE.

**Methods:**

Patients eligible to this multicenter prospective randomized phase II study are subjects aged from 18 years old suffering from colo-rectal liver metastases considered as resectable and with non-cirrhotic liver parenchyma. The primary objective is the percentage of change in FLR volume at 3 weeks after LVD or PVE using MRI or CT-Scan. Secondary objectives are assessment of tolerance, post-operative morbidity and mortality, post-hepatectomy liver failure, rate of non-respectability due to insufficient FLR or tumor progression, per-operative difficulties, blood loss, R0 resection rate, post-operative liver volume and overall survival. Objectives of translational research studies are evaluation of pre- and post-operative liver function and determination of biomarkers predictive of liver hypertrophy**.** Sixty-four patients will be included (randomization ratio 1:1) to detect a difference of 12% at 21 days in FLR volumes between PVE and LVD.

**Discussion:**

Adding HVE to PVE during the same procedure is an innovative and promising approach that may lead to a rapid and major increase in volume and function of the FLR, thereby increasing the rate of resectable patients and limiting the risk of patient’s drop-out.

**Trial registration:**

This study was registered on *clinicaltrials.gov* on 15th February 2019 (NCT03841305).

## Background

In patients undergoing major liver resection, portal vein embolization (PVE) has been widely used to induce hypertrophy of the non-embolized liver in order to prevent small-for-size and post-hepatectomy liver failure. PVE is a safe and effective procedure, but does not always lead to sufficient hypertrophy of the future liver remnant (FLR) [1]. Therefore, several approaches have been proposed to improve PVE:
i.combined technique with subsequent embolization of ipsilateral hepatic artery, was efficient for FLR hypertrophy, but has been abandoned regarding the increased risk of liver abscessii.intrahepatic biliary ablation using ethanol but seemed to increase the risk of damage to the bile ducts of the FLR;iii.the adjunct of hematopoietic stem cells to PVE, which is still under study.

Recently, the ALPPS (associating liver partition and portal vein ligation for staged hepatectomy) procedure has been developed by surgeons. Although a very high rate of liver hypertrophy has been reported [2], ALPPS was demonstrated to tremendously increase perioperative mortality and morbidity [3]. Another approach to improve FLR regeneration when insufficient after PVE consists in embolizing hepatic vein(s) [4]. Indeed, the sequential right hepatic vein embolization (HVE) after right PVE demonstrated an incremental effect on the FLR, but implies two different procedures with no time gain as compared to PVE alone. To optimize the phase of liver preparation before surgery, we developed the so-called liver venous deprivation (LVD) technique, a combination of PVE and HVE during the same intervention. We reported that LVD was safe and provided fast and important hypertrophy of the FLR at 3 weeks [5]. More recently, we showed that LVD could provide marked and very rapid increase not only in FLR volume but also in FLR function [6, 7] assessed with ^99m^Tc mebrofenin hepatobiliary scintigraphy with SPECT which has been validated as a quantitative method for evaluating liver function [8].

## Methods/design

### Aim of the study

The main objective of this randomized multicenter phase II trial is to compare the percentage of change in FLR volume at 3 weeks after LVD or PVE using MRI or CT-scan. Secondary objectives are listed in Table 1. Translational research objectives are i) evaluation of pre- and post-operative liver function and ii) determination of biomarkers predictive of liver hypertrophy**.**

**Table 1 Tab1:** Secondary objectives of the HYPER-LIV01 trial

Tolerance	
Post-operative mortality	
Post-operative morbidity	
Post-hepatectomy liver failure	
Rate of non-resectability due to insufficient FRL	
Rate of non-resectability due to tumor progression	
Per-operative difficulties (adhesions, pedicular dissection …)	
Blood loss, operating time, transfusions	
R0 resection rate	
Post-operative liver volume	
Overall survival	

### Sample size and follow-up period

Our hypotheses for sample size calculation are based on a systematic review on PVE before liver resection, involving 1791 patients [9]: the mean increase of the FLR volume was 37.9% at 26 days. In our preliminary study [5] and in a more recent paper by Le Roy et al. [10], a mean increase of 53% of the FLR volume was observed after 3 weeks. Therefore, it is realistic to expect a difference of 12% (or more) between the 2 procedures at 21 days. With a standard deviation of 14% in each arm, a two-sided α = 5% and a power of 90%, according to a Student Test, 30 patients have to be randomized by arm. Taking into account that 5% of the patients could not be evaluable, 32 patients have to be randomized per arm. Finally, planned enrollment will be 64 subjects. The expected duration of the recruitment of all patients is 24 months with a minimal duration of the subject participation of 5 months.

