#### Randomization

The randomization will be done according to the minimization method (ratio 1:1) and stratified on center and on type of resection scheduled (≤ 4 segments, > 4 segments). The standard arm is Portal Vein Embolization (PVE), the experimental arm is Liver Venous Deprivation (LVD). Figure 1 summarizes the design of the study.

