#### Study endpoints

The primary endpoint for the current trial is the percentage of change in future liver remnant (FLR) volume at 3 weeks after liver venous deprivation (LVD) or portal vein embolization (PVE) using MRI/CT-Scan. Secondary endpoints are listed in Table 2. Endpoints for the translational research are:
Evaluation of pre- and post-operative liver function. This will be evaluated using ^99m^Tc-mebrofenin scintigraphy through SPECT/CT acquisitions by calculating mebrofenin clearance in %/min/m^2^ of whole liver and FLR (described in [8]) at the same time points as CT/MRI (central review).To search for biomarkers predictive of liver hypertrophy (EGF, HGF, VEGF, H-EGF, TGF-beta, TNF-alpha, IL-10, IL-6, surviving, FGL-1). Blood samples will be stored by sponsor’s biological resource center (CRB MONTPELLIER). The biological studies on the samples will be managed by a biological committee and funded separately.

**Table 2 Tab2:** Secondary endpoints of the HYPER-LIV01 trial

Tolerance (toxicities are evaluated according to NCI-CTCAE version 4.03 published 14 June 2010)**.**	
Post-operative mortality defined as any death within 90 days after surgery or within the hospital stay.	
Post-operative morbidity defined as the percentages of grade I/II/II/IV/V complications according to the Clavien-Dindo classification within the 90 days after surgery or within the hospital stay.	
Post-hepatectomy liver failure defined according to the “50–50” criteria *(Balzan, Ann Surg 2005*) or peak bilirubin > 7 mg/dL *(Mullen, J Am Coll Surg 2007).*	
Rate of non-resectability due to insufficient FLR defined as the percentage of patients for whom resection will be not attempted due to insufficient FLR.	
Rate of non-resectability due to tumor progression defined as the percentage of patients for whom resection will not be attempted due to tumor progression.	
Rate of per-operative difficulties defined as the percentage of patients for whom per-operative difficulties are encountered by the surgeon (especially adhesions and challenging pedicular dissection or any other unscheduled surgical difficulties).	
Blood loss, operating time, transfusions. Blood loss (in mL), operating time (in minutes), transfusions (number of packed red blood cells) will be recorded.	
R0 resection rate defined as no microscopic tumor residual.	

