## Discussion

We developed an innovative trans-hepatic technique (called LVD) for both PVE and HVE, easy to practice by interventional radiologists. Hepatic vein(s) are accessed under US guidance using micropuncture sets and embolized using Amplatzer vascular plug(s) and cyanoacrylate for distal branches and veno-venous collaterals. In two preliminary studies [6, 7] we showed that LVD is safe (no migration of embolic material was observed) and provided a strong increase in both FLR volume and function at 3 weeks (respectively 52.6% (range, 1–175.6%) and 68.2% (range, 25.4–121.4%)). In a retrospective analysis, we also showed similar mortality/morbidity rates during and after surgery compared to PVE [11]. A paper from another team [12] studying LVD in association with biliary drainage in 6 patients with Klatskin tumors also showed no adverse events and a FLR hypertrophy of 67% (range 29–123) 3 weeks after the procedure. Given the high morbidity and mortality rate following ALPPS [3], LVD could be an attractive alternative technique to increase FLR volume in a short period of time and has the potential to replace PVE as a standard of care. This project also includes functional evaluations of both the whole liver and FLR using 99 m-Tc mebrofenin scintigraphy. This will bring additional useful data given the great potential of liver function to become a more accurate predictor of post-operative liver dysfunction than liver volume.

In conclusion, we believe that LVD is a promising method to improve liver preparation before major hepatectomy, thereby increasing the number of patients undergoing curative surgery and preventing drop-out due to tumor progression. This prospective, multicenter and randomized phase II trial is mandatory to confirm our preliminary results. Serial evaluations of liver function, based on 99 m-Tc mebrofenin scintigraphies, will be helpful to define the optimal time for resection.

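### The planning SD of 14% has no stated source and is hard to reconcile with the LVD spread in the article's own Discussion, so the 90% power rests on an unsupported input

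*Protocol article*

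**What the plan says.** In the protocol article, Study endpoints defines the outcome: "The primary endpoint for the current trial is the percentage of change in future liver remnant (FLR) volume at 3 weeks". Sample size and follow-up period takes a mean gain of 37.9% at 26 days for PVE from a systematic review. It takes 53% at 3 weeks for LVD from the team's preliminary study and one other paper. From these it concludes that "it is realistic to expect a difference of 12% (or more) between the 2 procedures at 21 days". The planning assumption on spread is "With a standard deviation of 14% in each arm", and with it "a two-sided α = 5% and a power of 90%, according to a Student Test, 30 patients have to be randomized by arm". An allowance of 5% for non-evaluable patients brings this to 32 per arm and 64 in total. The Methods part of the Abstract repeats the claim: the 64 patients are included "to detect a difference of 12% at 21 days in FLR volumes between PVE and LVD".

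The means carry citations. The SD does not.

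The Discussion reports spread for the same measure after LVD. Two preliminary studies by the team gave, for FLR volume and function at 3 weeks, "respectively 52.6% (range, 1–175.6%) and 68.2% (range, 25.4–121.4" (both in %). Another team's series of 6 patients with Klatskin tumours and biliary drainage gave "FLR hypertrophy of 67% (range 29–123) 3 weeks after the procedure". No SD or range for PVE appears anywhere in the article.

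**The concern.** If individual volume gains after LVD run from 1% to 175.6% around a centre near 53%, an SD of 14 puts the largest gain (175.6 − 52.6)/14 = 8.8 SDs above the centre and the smallest (52.6 − 1)/14 = 3.7 SDs below it. That is not what data with an SD of 14 look like in a series of ordinary size.

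The SD carries the whole sample-size argument, because the number of patients needed grows with its square. There is almost no slack. With a common SD, power at 30 per arm falls below 80% once the SD exceeds 16.3. What is at stake is whether the stated 90% power on the primary endpoint can be relied on when the result is read.

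**Working it through.** **1. Reproducing the plan.** Inputs from Sample size and follow-up period: difference 12, SD 14, two-sided 5%, 90% power, Student test; allocation 1:1 from Randomization.

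- Standard error with 30 per arm: 14 × √(2/30) = 3.615. Noncentrality: 12/3.615 = 3.32. Degrees of freedom: 58.
- Power from the noncentral t distribution is 90.4% at 30 per arm and 89.4% at 29, so 30 is right.
- 30/0.95 = 31.6, hence 32 per arm and 64 in total.

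The formula is not at fault. Only the SD is in question.

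**2. What the team's own LVD range permits.** For n patients with extremes a and b, the sample SD is smallest when all the others share one value. No distribution is assumed.

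- Range alone: smallest SD = (b − a)/√(2(n − 1)), with b − a = 175.6 − 1 = 174.6. Setting this to 14 gives n = 1 + 174.6²/(2 × 14²) = 78.8. The minimum is 14.07 at n = 78 and 13.98 at n = 79, so at least 79 patients are needed.
- If 52.6 is the mean: smallest SD = √[(51.6² + 123² + 71.4²/(n − 2))/(n − 1)], where 51.6 = 52.6 − 1, 123 = 175.6 − 52.6 and 71.4 = 123 − 51.6. This gives 30.8 at n = 20, 24.9 at n = 30, 19.1 at n = 50, 14.005 at n = 92 and 13.93 at n = 93. At least 93 patients are needed.

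These are floors, reached only if every patient except the two extremes has an identical gain. A realistic SD is higher. The article does not give the number of patients, so these n are assumptions.

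**3. The 6-patient series.** Here n is given.

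- Range alone: (123 − 29)/√(2 × 5) = 94/√10 = 29.7.
- If 67 is the mean: the deviations of the extremes are −38 and +56, and the other four must average −18/4 = −4.5. So √[(38² + 56² + 4 × 4.5²)/5] = 30.5.

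**4. Consequence for power, 30 per arm.** The 15.1-point column uses the gap between the cited means, 53 − 37.9. Standard error = √[(SD_PVE² + SD_LVD²)/30]; noncentral t, with Welch degrees of freedom where the SDs differ. The detectable difference at 90% power is about 3.30 to 3.33 times the standard error.

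| SD PVE / LVD | SE | Power, 12 points | Power, 15.1 points | Difference with 90% power |
|---|---|---|---|---|
| 14 / 14 (plan) | 3.61 | 90% | 98% | 11.9 |
| 14 / 20 | 4.46 | 75% | 91% | 14.7 |
| 14 / 25 | 5.23 | 61% | 81% | 17.3 |
| 14 / 30.5 | 6.13 | 48% | 67% | 20.3 |
| 14 / 40 | 7.74 | 33% | 48% | 25.8 |
| 20 / 20 | 5.16 | 63% | 82% | 17.0 |
| 25 / 25 | 6.45 | 45% | 63% | 21.3 |
| 30 / 30 | 7.75 | 33% | 48% | 25.5 |
| 40 / 40 | 10.33 | 21% | 30% | 34.0 |

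The first block leaves PVE at the planned value. The second gives PVE the same spread as LVD, for which the article has no evidence either way.

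**The case against.** The strongest defence is that the article does not prove 14% wrong.

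- **Unknown series size.** The range 1 to 175.6% comes with no number of patients, and the text does not say whether 52.6 is a mean or a median. With 79 or more patients (93 if it is a mean), an SD of 14 is arithmetically possible. This stands, and is why the point is that the figures are hard to reconcile, not that they are incompatible. Reaching 14 at those sizes would still require nearly all other patients to have the same gain.
- **Different sources.** The planning means are cited to other references than the ranges in the Discussion, and a condensed article may leave the SD's citation to the full protocol. This also stands, and the fix allows for it. It does not remove the tension between two statements about the same measure after the same procedure.
- **Different patients.** The 6-patient series concerns Klatskin tumours with biliary drainage, while the trial enrols non-cirrhotic patients with colorectal metastases and FLR below 30%. Six patients also estimate a trial's SD poorly. It is supporting evidence only.
- **LVD only.** No PVE spread is given, so the common-SD figures lend PVE the LVD spread. That is why the rows with PVE kept at 14 come first. Because the plan asserts 14 in each arm, doubt about LVD alone is enough to unsettle the 90%.

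A reader might go further and infer that the design has 33% power, or that a true benefit of 12 to 15 points would probably be missed. The article does not support either. The 33% needs SD 30 in both arms, or LVD at 40 with PVE at 14. At 15.1 points, power is 91%, 81% and 67% with PVE at 14 and LVD at 20, 25 and 30.5, and 82% with a common SD of 20; in those cases detection is more likely than not. Nor does the article say that a non-significant result would be read as no benefit. The choice of an unequal-variance test and the use of confidence intervals are details for the analysis plan, which is not shown.

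**Conclusion.** The point holds in this limited form. The calculation is correct, but its SD is given without a source, and the LVD data in the same article do not support it. The stated 90% power for 12 points with 30 per arm is therefore conditional on an SD of about 14 in both arms.

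The true power cannot be fixed from the document. Over assumed LVD SDs of 20 to 40 it runs from 75% down to 33% if PVE stays at 14, and from 63% down to 21% if both arms share the spread. For the 15.1-point gap the corresponding figures are 91% to 48% and 82% to 30%. The lower bounds on the SD are pure arithmetic; that the trial SD lies between 20 and 40 is an assumption. Confidence is high that 14% needs justification and moderate on how far power falls.

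**What to change.** Keep the 64 patients. In Sample size and follow-up period, either cite the source that supports 14% for this endpoint or replace it with one SD per arm, computed from the individual data of the team's own LVD and PVE patients. Then restate there, and in the Methods part of the Abstract, the power for 12 points and the difference detectable with 90% power, with a sensitivity range. Suggested wording, to be updated once the SDs are known: 30 evaluable patients per arm give 90% power for 12 points if the SD is 14 in both arms; with PVE at 14 and LVD between 20 and 40, power is 75% to 33% and the difference detectable with 90% power is about 15 to 26 points.

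The cost is a short recalculation, a few reworded sentences and a less favourable stated power. No patients are added and no procedure changes.

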### Selection of study population

#### Study population

Subjects aged from 18 years old suffering from liver metastases considered as resectable could be enrolled in this study if inclusion and exclusion criteria are satisfied.

#### Inclusion criteria

Patients eligible for inclusion in this study have to meet all the following criteria:
Liver metastases considered as resectable from colo-rectal origin (as validated by a multidisciplinary committee with at least one senior hepatic surgeon)Percentage of FLR volume < 30%Age ≥ 18 yearsGeneral health status WHO 0 or 1Estimated life expectancy > 3 monthsPatients whose biological parameters are:
Platelets ≥100,000/mm3,Polynuclear neutrophils ≥1000/mm3,Hemoglobin ≥9 g/dL (even transfused patients can be included)Creatininemia < 1.5 NBilirubinemia ≤2 NAST and ALT ≤5 NPT > 70%Reference liver CT-scan or MRI done during the 30 days preceding PVE or LVDWritten informed consentNational health insurance cover

#### Exclusion criteria

Patients eligible for this study must not meet any of the following criteria:
CirrhosisPresence of clinical ascitesOngoing participation or participation within the 21 days prior to inclusion in the study in another therapeutic trial with an experimental drugSerious non-stabilized disease, active uncontrolled infection or other serious underlying disorder likely to prevent the patient from receiving the treatmentPregnancy (βHCG positive), breast-feeding or the absence of effective contraception for women of child-bearing ageContraindication to MRI (in the following cases, a CT-scan must be used instead): Pacemaker or neurosensorial stimulator or implantable defibrillator, cochlear implant, ferromagnetic foreign bodyAllergy or contra-indication to iodine contrast agentsTreatment with anticoagulants (heparin or AVK) that cannot be interrupted for 48 hTreatment with anti-platelets that cannot be interrupted for 5 days for aspirin or clopidogrelLegal incapacity (persons in custody or under guardianship)Deprived of liberty Subject (by judicial or administrative decision)Impossibility to sign the informed consent document or to adhere to the medical follow-up of the trial for geographical, social or psychological reasons

#### Randomization

The randomization will be done according to the minimization method (ratio 1:1) and stratified on center and on type of resection scheduled (≤ 4 segments, > 4 segments). The standard arm is Portal Vein Embolization (PVE), the experimental arm is Liver Venous Deprivation (LVD). Figure 1 summarizes the design of the study.

**Fig. 1 Fig1:**
[figure not shown]
Study design of the HYPER-LIV01 trial

#### Study endpoints

The primary endpoint for the current trial is the percentage of change in future liver remnant (FLR) volume at 3 weeks after liver venous deprivation (LVD) or portal vein embolization (PVE) using MRI/CT-Scan. Secondary endpoints are listed in Table 2. Endpoints for the translational research are:
Evaluation of pre- and post-operative liver function. This will be evaluated using ^99m^Tc-mebrofenin scintigraphy through SPECT/CT acquisitions by calculating mebrofenin clearance in %/min/m^2^ of whole liver and FLR (described in [8]) at the same time points as CT/MRI (central review).To search for biomarkers predictive of liver hypertrophy (EGF, HGF, VEGF, H-EGF, TGF-beta, TNF-alpha, IL-10, IL-6, surviving, FGL-1). Blood samples will be stored by sponsor’s biological resource center (CRB MONTPELLIER). The biological studies on the samples will be managed by a biological committee and funded separately.

**Table 2 Tab2:** Secondary endpoints of the HYPER-LIV01 trial

Tolerance (toxicities are evaluated according to NCI-CTCAE version 4.03 published 14 June 2010)**.**	
Post-operative mortality defined as any death within 90 days after surgery or within the hospital stay.	
Post-operative morbidity defined as the percentages of grade I/II/II/IV/V complications according to the Clavien-Dindo classification within the 90 days after surgery or within the hospital stay.	
Post-hepatectomy liver failure defined according to the “50–50” criteria *(Balzan, Ann Surg 2005*) or peak bilirubin > 7 mg/dL *(Mullen, J Am Coll Surg 2007).*	
Rate of non-resectability due to insufficient FLR defined as the percentage of patients for whom resection will be not attempted due to insufficient FLR.	
Rate of non-resectability due to tumor progression defined as the percentage of patients for whom resection will not be attempted due to tumor progression.	
Rate of per-operative difficulties defined as the percentage of patients for whom per-operative difficulties are encountered by the surgeon (especially adhesions and challenging pedicular dissection or any other unscheduled surgical difficulties).	
Blood loss, operating time, transfusions. Blood loss (in mL), operating time (in minutes), transfusions (number of packed red blood cells) will be recorded.	
R0 resection rate defined as no microscopic tumor residual.	
Pre- and post-operative liver volumes: This will be evaluated through CT or MRI acquisitions by calculating whole liver, tumor and FRL volumes at week 2, 3 then every 2 weeks until surgery or week #7, and 4 weeks after surgery (central review).	
Overall survival defined as the time from date of randomization to date of death from any cause. Patients alive will be censored at the date of last news.	

